## Abstract

**Background:**

Insomnia is one of the most common symptoms among breast cancer patients, which can be present throughout all stages of breast cancer. As a non-pharmacological alternative treatment, acupuncture has been suggested to improve sleep situations in patients with cancer suffering from insomnia. However, there is a lack of well-designed, high-quality clinical evidence regarding the efficacy of acupuncture in the treatment of breast cancer-related insomnia. This study is conducted to evaluate the efficacy and safety of acupuncture treatment for breast cancer-related insomnia.

**Methods:**

This study was designed as a multicenter, randomized, sham-controlled clinical trial. A total of 264 eligible patients with breast cancer-related insomnia will be randomized into an acupuncture group and a sham acupuncture group in a 1:1 ratio. In the trial, patients in the acupuncture and sham acupuncture groups will receive 12 sessions over a consecutive 4-week period. The primary outcome will be the treatment response rate of Insomnia Severity Index (ISI) at week 4; secondary outcomes include treatment remission rate of ISI, Sleep Efficiency (SE) obtained by the use of Sleep diary, treatment response rate of ISI at 8th and 16th weeks of follow-up, the mean changes of ISI, Generalized Anxiety Disorder Scale (GAD-7), Patient Health Questionnaire-9 (PHQ-9), Quality of Life Questionnaire - Core 30 (QLQ-C30), sleep parameters recorded in Actigraphy and weekly usage of remedial drugs. Adverse events will be recorded throughout the study. All analyses will be based on the ITT principle and performed with SAS 9.4 statistical software.

**Discussion:**

This trial will evaluate the clinical efficacy and safety of acupuncture for breast cancer-related insomnia. If proven effective, acupuncture will provide an effective option for patients with breast cancer-related insomnia, which will play a positive role in helping patients reduce their use of sleeping medications.

**Clinical trial registration:**

ClinicalTrials.gov, identifier NCT05510700.

## Background and objective

Insomnia is one of the most common symptoms among cancer patients. It usually refers to sleep disorders that occur among cancer patients, mainly including reduced total sleep time, difficulty in falling asleep, discontinuous sleep, easy early awakening, and inability to continue sleeping after waking up (1–5). It has been reported that about 36%-59% of cancer patients have been accompanied by insomnia at some time in their cancer trajectories (6). Insomnia may occur throughout all stages of the cancer pathways and is significantly associated with poor psychological status, physiological functioning, quality of life, increased inflammation, and possible disease progression and survival in cancer patients (7–12).

Breast cancer is one of the most common malignancies affecting women’s health, with the highest prevalence among cancers related to females (13, 14). In addition, among the various malignancies, breast cancer patients have the highest prevalence of insomnia, ranging from 42% to 69% (6), which is almost twice as high as that of the general population (6, 7, 15). Breast cancer-related insomnia, which often leads to fatigue and depression, is even associated with the risk of death (16, 17). Sick leave, unemployment, radiation, chemotherapy, and side effects of cancer treatment are all important factors contributing to insomnia in breast cancer patients (18–20). Currently, pharmacotherapy remains the most common treatment for patients with breast cancer-related insomnia (21). However, medication is only deemed beneficial for a short period (22), and long-term use will have negative effects. Although cognitive behavioral therapy (CBT) has made considerable progress in recent years (23), the use of CBT in cancer patients is complex (24) and limited. Consequently, it has become clinically crucial to figure out how to properly handle insomnia in breast cancer survivors and improve their quality of life. Fortunately, acupuncture therapy, which has a long history of use in the treatment of insomnia, has accumulated a wealth of expertise.

Acupuncture stemming from ancient theories and wisdom, has been used in the treatment of disease for thousands of years. In recent years, acupuncture has been used as a non-pharmacological intervention for the treatment of insomnia to improve clinical symptoms in patients with insomnia (25–27). It has been shown that acupuncture can increase sleep quality while addressing symptoms of mental and emotional distress (28). Additionally, acupuncture is now being used to improve patients’ sleep problems in cancer centers (29, 30). Although there have been a few clinical reports about acupuncture for cancer-caused insomnia (31–33), these studies fail to classify different types of cancer, and have small sample sizes, or the subjects come from a single center. A systematic evaluation of randomized clinical trials on acupuncture for cancer-related insomnia also has pointed out that the current level of evidence is low, that the number of clinical studies is small, and that the clinical guidance is limited, thus definite conclusions cannot be drawn (34). Therefore, high-quality clinical studies are needed to verify the clinical effectiveness of acupuncture for breast cancer-related insomnia.

In this trial, we will use a multicenter, randomized, controlled study to evaluate the clinical efficacy and safety of acupuncture in the treatment of breast cancer-related insomnia; we will make a comprehensive assessment of patients’ sleep from both subjective and objective levels. Meanwhile, we will also focus on the clinical onset time of acupuncture to observe whether acupuncture can improve patients’ sleep and alleviate breast cancer-related insomnia in short-term treatment.

This study hypothesizes that acupuncture will effectively alleviate insomnia symptoms in breast cancer patients, potentially reducing the need for sleeping medications. This study aims to provide robust evidence supporting acupuncture’s clinical benefits and informing treatment strategies for breast cancer-related insomnia.

## Methods

### Study design

This study is a multicenter, randomized, single-blind, sham acupuncture controlled trial, which will be conducted at 6 centers, including LongHua Hospital Shanghai University of Traditional Chinese Medicine, Yueyang Hospital of Integrated Traditional Chinese and Western Medicine of Shanghai University of Traditional Chinese Medicine, Shanghai Seventh People’s Hospital, Hainan Traditional Chinese Medicine Hospital, Affiliated Hospital of Jiangxi University of Traditional Chinese Medicine, and Xuhui District Central Hospital of Shanghai. The study has been approved by the Medical Ethics Committee of LongHua Hospital Shanghai University of Traditional Chinese Medicine (No. 2022LCSY032) and registered at ClinicalTrials Registry (NCT05510700). We will recruit 264 patients who meet the inclusion criteria and assign them to the acupuncture and sham acupuncture groups in a 1:1 ratio. The treatment will last 4 weeks in both groups, followed by a 12-week follow-up. A flow chart of the trial procedures is illustrated in **Figure 1** and **Table 1** with a detailed description of the study procedures and data collection.

**Figure 1 f1:**
[figure not shown]
Trial flow chart. ISI, Insomia Severity Index; GAD-7, generalized Anxiety Disorder Scale; PHQ-9, Patient health Questionnaire-9; QLQ-C3O, Quality of Life Core Scale; SE, Sleep Efficiency.

**Table 1 T1:** Schedule of enrolment, interventions and assessments.

Study period	Enrolment		Intervention period				Follow-up period	
Time point	Week -1	Week 0	Week 1	Week 2	Week 3	Week 4	Week 8	Week 16
Eligibility screening	**×**							
Sign informed consent	**×**							
Medical history	**×**							
Randomization		**×**						
**Intervention**								
Acupuncture			**×**	**×**	**×**	**×**		
Sham acupuncture			**×**	**×**	**×**	**×**		
**Primary outcomes**								
Treatment response rate						**×**		
**Secondary outcomes**								
Treatment remission rate						**×**	**×**	**×**
Treatment response rate							**×**	**×**
The mean changes of ISI						**×**	**×**	**×**
SE with Sleep diary		**×**	**×**	**×**	**×**	**×**		
GAD-7		**×**				**×**		
PHQ-9		**×**				**×**		
QLQ-C30		**×**				**×**		
Actigraphy sleep assessment		**×**	**×**			**×**		
Adverse events			**×**	**×**	**×**	**×**		
Weekly usage of remedial drugs			**×**	**×**	**×**	**×**	**×**	**×**
**Success of blinding**						**×**		

### Patient recruitment

All participants for this project will come from the six research centers mentioned above. Participant recruitment will be conducted through posting announcements and posters on the official web-based information platforms. Interested participants can contact researchers for initial screening through the phone numbers provided in the recruitment. Participants who initially meet the inclusion criteria will then be interviewed face-to-face and assessed at baseline with an independent researcher. After being screened by the investigators according to inclusion and exclusion criteria, subjects who meet the inclusion criteria will be informed that they will be randomly assigned to the acupuncture group or the sham acupuncture group. In addition, they will be informed of the possible benefits and risks of the study. Before entering the study, they will voluntarily sign a written informed consent, and they are free to withdraw at any time during the study.

### Inclusion criteria

The eligibility criteria that participants meet for the trial are as follows (1): Meet the diagnostic criteria for breast cancer in the 2022 2^nd^ edition of the National Comprehensive Cancer Network (NCCN) Clinical Practice Guidelines in Oncology and the American Joint Committee on Cancer (AJCC) Cancer Staging Manual (8th edition) for breast cancer staging criteria, meet the diagnostic criteria for breast cancer with TNM stage I to III; meet the diagnostic criteria for insomnia disorder within the Diagnostic and Statistical Manual of Mental Disorders, 5th Edition (DSM-5) (35): Insomnia occurred on a minimum of three nights per week and persisted for at least one month, and was related to the cancer itself or cancer-related treatment happened after breast cancer diagnosis (2). female patients aged 18–75 years (3). Eastern Cooperative Oncology Group (ECOG) performance status ≤ 2 (range, 0–5, with higher scores indicating a poorer physical condition) (4). ISI ≥ 8 (range, 0–28, with higher scores suggesting more severe insomnia) (36). (5) Predicted survival of ≥ 6 months. (6) Patients had never received acupuncture treatment. (7) No mental or intellectual abnormalities, able to understand the provisions of the scales and complete the assessment. (8) Consent to participate in this study and sign a written informed consent.

### Exclusion criteria

Patients who meet any of the following criteria are excluded from treatment: (1) Combination of more serious heart, liver, kidney, and other major diseases. (2) Patients who are pregnant or breastfeeding. (3) Those with planned surgery during the trial. (4) Previous history of drug abuse or addiction. (5) Those who have taken sedative-hypnotic drugs or antipsychotic drugs 2 weeks before the baseline visit, or received other treatment for insomnia (e.g., cognitive behavioral therapy, etc.) 3 months before the baseline visit, which may affect the efficacy of the observation. (6) Insomnia due to cancer pain with a numeric rating scale (NRS) score ≥ 4, or insomnia due to other physical diseases. (7) Long-term night work or irregular relaxation. (8) Ulcers, abscesses, skin infections, etc. at the site of needling. (9) Participation in other clinical medical trial studies within the last month.

### Randomization, allocation concealment and blinding

The random assignment scheme for this study will be generated by the Clinical Research Center of LongHua Hospital Shanghai University of Traditional Chinese Medicine with the use of the “Proc plan” program of SAS 9.4 statistical analysis software. The central randomization scheme will utilize stratified block randomization with centers as a stratification factor, competing for group inclusion. Centers notify the data management center when blocks are depleted for replenishment. Treatment assignment codes will be placed in sequentially numbered opaque envelopes by independent investigators. The envelopes will be selected by the staff members according to the order of the patients’ visits. All participants will be informed that they have an equal chance of being assigned to the acupuncture or sham acupuncture groups. Participants and researchers will not be able to anticipate groupings. In addition, to ensure shielded implementation, all investigators will receive training in the normative implementation of this study several times before the experiment is implemented, with strict adherence to the departmental separation principle.

The single-blind method is used in this trial. Except for the acupuncturist, all participants, outcome assessors, data analysts, and statisticians will be blinded during the study. We will strictly demand that communication among subjects be limited during treatment. In addition, we will schedule appointments. For the blind method to be successful, patients must wear eye masks during treatment and it is performed in a closed treatment unit. Moreover, all participants will be asked to guess which treatment they received after their last treatment to assess the success of the blinding method.

### Intervention

Participants in both groups will be given sleep hygiene instructions (e.g., be careful to avoid coffee, tea, alcohol, etc., maintain a routine, and appropriate sleep environment, and also pay attention to emotional self-regulation, etc.) through conversation, and will use it as the basic treatment of breast cancer-related insomnia. The conversations will be conducted at baseline, weeks 1, 2, 3 and 4. Meanwhile, participants will be instructed to keep a sleep diary for 5 weeks - weeks 0, 1, 2, 3 and 4. All participants will receive three treatments per week (every other day), each lasting for 30 minutes, which amounts to 12 sessions over the 4-week course. Follow-up time is week 4 and week 12 after treatment (ie, week 8 and week 16 of the whole trial period). These treatments will be administered following skin sterilization. The patients will be asked to remain supine and wear an eye mask throughout the treatment.

If patients have severe physical discomfort caused by insomnia for 2 or more consecutive days, they can take medication for sleep disorders according to their conditions, no matter what type, brand and dose, but they are required to strictly record the name, dose, and frequency of medication. Meanwhile, the investigators will meticulously document the patient’s medicine on a case report form (CRF).

### Acupuncture group

Participants in the treatment group will receive acupuncture treatment at Nei Guan (PC 6), Shen Men (HT 7), Shen Ting (GV 24), Yin Tang (GV 29), Zhong Wan (CV 12), San Yin Jiao (SP 6), Zhao Hai (KI 6), and Shen Mai (BL 62). Among the above acupoints, Nei Guan (PC 6), Shen Men (HT 7), San Yin Jiao (SP 6), Zhao Hai (KI 6), and Shen Mai (BL 62) are applied bilaterally while the rest are applied on the anterior midline (**Figure 2**). (Acupoint Location: refer to *The Location of Acupoints: State Standard of the People’s Republic of China* [GB/T 12346–2021]). The acupuncture technique for each point is described in **Table 2**. As acupuncture needles are inserted, all needles will be lifting, twirling, and thrusting to reach *de qi*, a sensation generally associated with acupuncture, including swelling, soreness, numbness, and heaviness, which is considered as an important factor in acupuncture’s therapeutic effect (37). In the study, sterile acupuncture needles will be used, which are from Suzhou Medical Supplies Factory Co.’s Huatuo (size 0.25*25mm and 0.25*40mm).

**Figure 2 f2:**
[figure not shown]
location of Acupoints for the acupuncture and Sham acupuncture Groups. PC 6; Nei Guan; HT 7: Shen Men; GV 24: Shen Ting; CV 12; Zhong Wan; SP6: san Yin Jiao; K16: Zhao Hai; BL 62: Shen Mai.

**Table 2 T2:** The locations and manipulations of acupoints in the intervention group.

Acupoint	Location	Manipulation
Nei Guan (PC 6)	On the anterior side of the forearm, 2 *cun* above the transverse stripe of the distal palmar aspect of the wrist, between the palmaris longus tendon and the radial carpal flexor tendon.	Insert the needle perpendicularly for 0.5–1.0 *cun*.
Shen Men (HT 7)	On the anteromedial side of the wrist, the ulnar end of the palmar wrist crease, and the radial border of the flexor carpi ulnaris tendon.	Insert the needle perpendicularly for 0.3–0.5 *cun*.
Shen Ting (GV 24)	On the head, 0.5 *cun* straight above the middle of the front hairline.	Insert the needle transversely for 0.5–0.8 *cun*.
Yin Tang (GV29)	At the midpoint between the medical ends of the eyebrows.	Insert the needle transversely for 0.3–0.5 *cun*.
Zhong Wan (CV 12)	On the upper abdomen, 4 *cun* above the umbilicus, on the anterior midline.	Insert the needle perpendicularly for 1.0–1.5 *cun*.
Zhao Hai (KI 6)	On the medial side of the foot, 1 *cun* below the tip of the medial malleolus, in the depression at the lower edge of the medial malleolus.	Insert the needle perpendicularly for 0.5–0.8 *cun*.
San Yin Jiao (SP 6)	On the inner side of the calf, 3 *cun* above the tip of the medial malleolus, on the posterior border of the medial tibia.	Insert the needle perpendicularly for 1.0–1.5 *cun*.
Shen Mai (BL 62).	On the lateral side of the foot, directly below the tip of the lateral malleolus, in the depression between the lower edge of the lateral malleolus and the calcaneus.	Insert the needle perpendicularly for 0.3–0.5 *cun*.

### Sham acupuncture group

To match the true acupuncture points, sham points 1 *cun* lateral to Nei Guan (PC 6), Shen Men (HT 7), Shen Ting (GV 24), Yin Tang (GV 29), Zhong Wan (CV 12), San Yin Jiao (SP 6), Zhao Hai (KI 6), and Shen Mai (BL 62) will be used. As with the acupuncture group, sham points of Nei Guan (PC 6), Shen Men (HT 7), San Yin Jiao (SP 6), Zhao Hai (KI 6), and Shen Mai (BL 62) are applied bilaterally while the rest are applied unilaterally 1 *cun* left to the anterior midline (**Figure 2**). The placebo needles selected for this study are blunt needles without a sharp tip that cannot be pierced into the skin. The placebo needles are from Guizhou Andi Medical Equipment Co., with a size of 0.25*25mm. Meanwhile, an external patch device will hold the needles in place and these needles visually appear to be pierced into the skin. This manipulation of the placebo needles has been validated as feasible in previous clinical studies (38). At the end of the treatment, the acupuncturist will press the acupuncture point with a dry cotton ball to allow the patient to feel the “needles” being pulled out. It is worth pointing out that the sham acupuncture device used in this study has been patented by China National Intellectual Property Administration (Patent Number: ZL 2023 2 0605629.3).

## Outcomes

### Primary outcome

The Primary outcome is the treatment response rate (39, 40), which is the percentage of people whose ISI score decreased by ≥8 points at the end of week 4 treatment compared to the baseline score.

As a subjective and validated measure, the Insomnia Severity Index (ISI) assesses various aspects of sleep, including the onset of sleep, maintenance, early awakening, dissatisfaction, interference with daytime functioning, life quality, and mental distress. The scores are 0 to 4, with a total score range from 0 to 28. Higher scores indicate more severe insomnia. ISI levels can be classified as absence of insomnia (0 to 7), sub-threshold insomnia (8 to 14), moderate insomnia (15 to 21), and severe insomnia (22 to 28).

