### Secondary outcome

The secondary outcomes include the following eight items (1): Treatment remission rate of ISI (40): The percentage of people with a total score of <8 points in total ISI score compared to the baseline score. It will be evaluated at weeks 4, 8 and 16. (2) SE with Sleep Diary: SE is the percentage of time spent asleep while in bed (41). It is calculated by (TST/TIB) × 100%. Sleep diary analysis will be used to determine SE subjectively which will be assessed at weeks 0, 1, 2, 3 and 4. Sleep Onset Latency (SOL), Wake After Sleep Onset (WASO), Early Morning Awakening (EMA), and Total Time in Bed (TIB) are among the sleep metrics that may be monitored using a sleep diary (41). (3) Treatment response rate of ISI at the 8th and 16th weeks of follow-up. (4) The mean changes of ISI (40) from baseline. It will be evaluated at weeks 4, 8 and 16. (5) GAD-7 (42): It is a concise anxiety self-assessment instrument consisting of 7 items to assess patients’ anxiety over the past two weeks. It will be evaluated at weeks 0 and 4. (6) PHQ-9 (43): It is a simple and validated 9-item depression self-assessment tool that assesses patients’ depression over the past two weeks. It will be evaluated at weeks 0 and 4. (7) QLQ-C30 (44): It contains 30 entries with six dimensions. It is widely used in clinical studies to assess the life quality of patients. It will be evaluated at weeks 0 and 4. (8) Sleep parameters recorded in Actigraphy (wGT3X-BT. LLC, Pensacola, USA): It provides a non-invasive monitoring method (45) that allows objective data related to sleep quality to be collected in the subject’s relatively usual and familiar natural sleep environment. It records the contents of TST, sleep awakenings (SA), WASO, average wake duration (AA) and SE, with the detection and interpretation of movements using the device’s accelerometer. We used the default settings of ActiLife for sleep situations: a sampling rate of 30 Hz in a time window of 60s (46). It will be evaluated at weeks 0, 1 and 4. (9). Weekly usage of remedial drugs: It is the percentage of participants who used emergency drugs. It will be evaluated at weeks 1, 2, 3, 4, 8 and 16.

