### Sample size calculation

In this study, the sample size is estimated according to the treatment response rate of subjects at week 4 as the primary outcome indicator (40, 41). Based on the results of our pre-preliminary trial, the treatment response rate at week 4 was 33.3% (5/15) in the treatment group; 6.7% (1/15) in the control group; we conservatively assumed a treatment response rate of 27% at week 4 in the treatment group and 10% at week 4 in the control group. The sample size was calculated by using the “Tests for Two Proportions (Test Version)” module of PASS15 software (NCSS, LLC. Kaysville, Utah, USA) with a one-sided alpha = 0.025, power of 90%, and a 1:1 ratio. In each group, 105 cases will be needed. Considering the lost and rejected cases of 20%, the final minimum number of subjects required for the treatment and control groups will be 132 cases each, and a total of at least 264 subjects will be included.

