### Statistical methods

Data will be collected for each study subject at a series of dynamic time points by the use of standardized and structured questionnaires. And then three databases will be created for this study, which are the Full analysis set (FAS), the Per-protocol set (PPS), and the Safety set (SS). For each study group of the trial, missing values were filled using the last observation carryover method, i.e., data from the last obtained data for the missing visit to the end of the observation at all time points. Statistical analyses will be performed using SAS 9.4 software (SAS Institute Inc., Cary, North Carolina 27513, US). Continuous variables are expressed as mean ± standard deviation or median (interquartile range), and categorical variables are represented by frequency (constitutive ratio). The significance level will be set at 5% (*p* < 0.05) with a 95% confidence interval.

(1) Data analysis of primary outcome: The primary outcome in the study is the treatment response rate, which is qualitative data. The treatment response rate at week 4 will be compared between the two groups by the CMH (Cochran’s and Mantel-Haenszel statistics) test, to ensure the effects of different treatment factors on the treatment response rate.(2) Data analysis of secondary outcome: Among the secondary indexes, treatment response rate, treatment remission rate, SE with sleep diary and actigraphy, and weekly usage of remedial drugs are all qualitative data measured repeatedly, so generalized estimating equations will be used for statistics. The mean changes of ISI, SOL/WASO/EMA/TST in sleep diary, TST/SA/WASO/AA in Actigraphy, GAD, PHQ and QLQ-C30 scale are all quantitative data, therefore mixed-effects models will be used for statistics.(3) Data analysis of safety indicators: the incidence of adverse events and medication use are qualitative data, so the chi-square test or Fisher’s test will be used for statistics.

In the process of baseline data collection before conducting the study, we added some covariates, such as anxiety, depression, age, and treatment of breast cancer. When the whole study is completed, *post hoc* analysis will be done to compare the therapeutic effects among different subgroups. To be specific, the stratified CMH test will be used to test the therapeutic effect of acupuncture on cancerous insomnia in different subgroups of breast cancer treated with different therapeutic schedules (e.g. radiotherapy, chemotherapy).

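### The primary responder test should use baseline ISI and centre, and the already planned week-4 ISI change should be named the key secondary outcome

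*Protocol article*

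**What the plan says.** All references are to the protocol article; no separate SAP is at hand.

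- **Primary outcome:** the response rate, "which is the percentage of people whose ISI score decreased by ≥8 points at the end of week 4 treatment compared to the baseline score". The ISI is described "with a total score range from 0 to 28", with bands 0-7, 8-14, 15-21 and 22-28. Two citations support the definition.
- **Statistical methods, item (1):** "The treatment response rate at week 4 will be compared between the two groups by the CMH" test. No stratification variable or covariate is named for it.
- **Inclusion criteria:** ISI of 8 or more.
- **Randomization, allocation concealment and blinding:** stratified blocks, with centre as the stratification factor (six centres).
- **Sample size calculation:** "we conservatively assumed a treatment response rate of 27% at week 4 in the treatment group and 10% at week 4 in the control group", one-sided alpha 0.025, 90% power, 105 per group, 132 after 20% loss. The pilot rates were 5/15 and 1/15. No mean, SD or distribution of the ISI change is given.
- **Secondary outcome, item (4):** "The mean changes of ISI (40) from baseline. It will be evaluated at weeks 4, 8 and 16". Statistical methods assigns it a mixed-effects model. No ranking of secondary outcomes is stated.

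**The concern.** Once the ISI change is reduced to responder or non-responder, a fall of 7 counts the same as a worsening, and a fall of 8 the same as a fall of 20. That makes it more important that the test uses what is known about each patient at entry. How much a patient can improve depends on where she starts, so baseline ISI is a natural predictor of response. It is collected in everyone and has bands the protocol itself defines. Centre determined the allocation lists, and an analysis that follows the randomisation should carry it.

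If neither enters the test, chance imbalance in baseline severity between arms goes uncorrected in the headline comparison, and some precision is given away for nothing. Separately, the full-scale ISI change holds more information than the cut. Its place among several unranked secondary outcomes leaves it without a defined role beside the primary result.

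**Working it through.** **1. The plan's own sample size.** Inputs from Sample size calculation: p1 = 0.27, p2 = 0.10, one-sided 0.025, power 90%.

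- Unpooled formula: n = (1.960 + 1.282)² × (0.27×0.73 + 0.10×0.90) / 0.17² = 10.507 × 0.2871 / 0.0289 = 104.4, so 105 per group. This matches. The pooled formula gives 108.
- Loss of 20%: 105 / 0.80 = 131.25, so 132. This matches.
- Power of the two-proportion test (pooled): 89.3% at 105 per arm and 94.9% at 132. Exact enumeration at 105 gives 90.2%.

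The trial is therefore sized to its 90% target for response.

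**2. What the 8-point rule asks at each entry score** (cut from Primary outcome, entry rule from Inclusion criteria).

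| Entry ISI | Week-4 ISI needed to respond | Remark |
|---|---|---|
| 8 | 0 | only a perfect score counts |
| 10 | 2 or less | ending at 3 is in the 0-7 band but is non-response |
| 14 | 6 or less | must leave the insomnia range |
| 24 | 16 or less | 16 is still in the 15-21 band but is response |

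**3. What using baseline ISI gains.** Simulation with integer ISI, entry 8-28, floor at 0, 105 per arm, calibrated to 27% and 10%, five assumed scenarios (baseline means 15-19), 3,000 runs each:

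- CMH without strata: 89.4-90.2%.
- CMH stratified by ISI class: 89.5-91.4%.

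The change was negligible where response did not depend on baseline and up to about 2 points where it did. The Monte Carlo standard error of one power figure is √(0.9×0.1/3000) = 0.55 points, so changes below about one point should not be read closely. These figures concern ISI-class strata only, not centre.

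**4. The full-scale alternative.** This needs an assumption that the protocol does not make: a normal ISI change with the same SD in both arms.

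- Implied shift: d = z(0.90) − z(0.73) = 1.2816 − 0.6128 = 0.669 SD.
- Power = Φ(d√(n/2) − 1.96). At 105: Φ(4.845 − 1.96) = 99.8%. At 132: Φ(5.433 − 1.96) = over 99.9%.
- n for 90% power: 2 × 10.507 / 0.669² = 47 per arm (48 with the t distribution), against 105.

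The gain is about 10 points at 105 per arm and about 5 at 132.

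Now let the acupuncture SD be r times the sham SD, holding 27% and 10%. Then the shift is m = 1.2816 − 0.6128r, the SD is s = √((1 + r²)/2), and m/s replaces d (105 per arm):

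| r | m/s | Power, ISI change | Against about 90% for response |
|---|---|---|---|
| 1.0 | 0.669 | 99.8% | about +10 |
| 1.1 | 0.578 | 98.7% | about +9 |
| 1.2 | 0.494 | 94.8% | about +5 |
| 1.3 | 0.418 | 85.8% | about −4 |
| 1.5 | 0.284 | 54.0% | about −36 |

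If instead only a subset improves, by 8, 10 or 12 points, power on the ISI change is 91.0%, 88.2% and 87.9%, in effect no gain.

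Under equal SDs a smaller true effect widens the gap: 22% vs 10% gives 66% (response) against 96% (change), and 20% vs 10% gives 53% against 89%. These figures rest on the same assumption and were not varied for unequal SDs or a responding subset.

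**The case against.** **The strata may be in the SAP.** A CMH test is by nature a stratified method, and a journal article commonly leaves its strata to the analysis plan. This stands: the article does not say that baseline ISI and centre are excluded, only that the test is named without them. If the SAP already names both, this part of the point is met.

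**The gain is small.** This also stands. Zero to 2 points would not justify a costly change. It does justify a line of analysis text.

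**Stronger readings that the documents do not support:**

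- A reader might infer that the trial loses about 10 points of power under its own assumptions. It assumes two response rates and nothing about the distribution of change. The 10 points come from an added equal-SD model at 105 per arm, and the sign depends on that model. Since the abstract promises analysis by the ITT principle and missing values are carried forward, the analysed number may be nearer 132, where the gap is about 5 points.
- A reader might infer that the trial is underpowered. It meets its 90% target for the outcome it chose.
- A reader might infer that the full-scale information is discarded. The week-4 ISI change is a planned secondary outcome with a mixed model, and its place in an unranked list carries no weight.
- A reader might infer that the cut is unjustified. It rests on cited sources that cannot be judged here, and a responder rate and a mean difference answer different clinical questions.

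**Replacing the primary outcome is not cheap.** The trial is registered, recruitment began in February 2023, and the acupuncturists are unblinded. A switch invites a charge of outcome switching and removes the basis of the sample size, with no SD available to write a new one. This stands, and is why replacement is not the recommendation.

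**Conclusion.** The point holds in limited form. The primary test, as described, does not mention the baseline score that sets what an 8-point fall requires, nor the randomisation stratum. Using both is good practice at almost no cost. The expected change in power from ISI-class strata is about zero to +2 points from roughly 90%. It rests on assumed baseline distributions and on how strongly response depends on baseline, which the documents do not give.

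The larger efficiency argument is conditional. With an equal-SD normal change, the ISI change would have over 99% power at 105 per arm against about 90% for response (over 99.9% against about 95% at 132). At 105 per arm the advantage halves at an SD ratio of 1.2, becomes a loss by 1.3, and disappears if only a subset benefits. The protocol does not say which pattern to expect. That supports a defined role for the ISI change beside the primary outcome, not a finding that the choice of primary outcome is wrong.

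**What to change.** 1. Keep response at week 4 as the primary outcome. State that it is tested by a CMH stratified by centre and baseline ISI class (8-14, 15-21, 22-28), or by logistic regression on treatment, baseline ISI and centre. Choose one before unblinding.
2. Check sparsity before choosing. Six centres by three classes make 18 strata, or about 12 patients each with 210 analysed (210/18 = 11.7). The planning rates give about 39 responders (105×0.27 + 105×0.10 = 38.85). If the CMH is chosen, fix a rule in advance for merging sparse strata.
3. Name the week-4 ISI change, adjusted for baseline ISI and centre, as the first (key) secondary outcome, using the week-4 contrast of the planned mixed model or an ANCOVA.
4. Optional, for the sponsor to weigh: make the ISI change primary by amendment before unblinding, with response as first secondary. This needs a stated SD, a new sample size rationale, a registry update and an explanation of the change.

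Items 1 to 3 need only analysis wording (in the SAP, if it does not already say this) and no new data, visits or patients. Item 4 carries the cost of changing a registered primary outcome in a running trial.
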